#### Items to record and schedule

Patient information during initial diagnosis of prostate cancer including the following:date of birth, diagnosis date, age, PSA level, Gleason score, clinical stage, metastatic sites, and rate of bone metastasesPatient information during registration (Table. 1):Patient background data: institution ID, registration date, date of birth, age, height, body weight, PS, concomitant disease, blood sampling (PSA, serum testosterone, white blood cell (WBC), red blood cell (RBC), alkaline phosphatase (ALP), and lactate dehydrogenase (LDH), among others)Imaging: computed tomography (CT) and bone scintigraphy shall be performed on registration to verify metastatic sitesQOL (FACT-P)Follow-up after registration (Table. 1);Blood sampling (PSA, WBC, RBC, ALP, and LDH, among others): every monthAEs as classified according to the CTCAE ver. 4.0: every monthImaging test: CT and bone scintigraphy when progressive disease is suspectedQOL (FACT-P): every 3 months

**Table 1 Tab1:** Follow-up schedule of examination

	Baseline	1 month	2 months	3 months	Every 1 month	Every 3 months	Discontinuation of therapy
Informed consent	○						
Medical history	○						
Confirmation of eligibility criteria	○						
Randomization	○						
Serum testosterone	○						
FACT-P	○	–	–	○	–	○	○
PSA^a^	○	○	○	○	○	○	○
Biochemical examination^a^	○	○	○	○	○	○	○
CT, bone scintigraphy	○	When progressive disease is suspected^b^					○
Safety	○	○	○	○	○	○	○
Further therapy	–	–	–	Best standard care			

^a^After the discontinuation of enzalutamide or flutamide, PSA and biochemical examination will be continued until September 2018

^b^When progressive disease is suspected, CT and bone scintigraphy will be performed to confirm radiographic disease progression

#### Study period

Registration period: 3 years and 3 months (January 2015–March 2018).

Follow-up period: 6 months after the last patient registration.

#### Ethical consideration and study registration

The study will be performed in accordance with the Declaration of Helsinki and will comply to the International Conference on Harmonization and Good Clinical Practice. All possible treatments and examinations for CRPC are undertaken after obtaining written informed consent from the patients before registration. The OCUU-CRPC study received approval from the institutional ethics committees of the participating institutions. The study has been registered at clinicaltrials.gov (NCT02346578) and the University Hospital Medical Information Network (UMIN000016301).

### Calculation of the target sample size

We hypothesize that the PSA response rate (PSA reduction by ≥50%) of enzalutamide at 3 months is 75%. According to the PREVAIL study [16], the best PSA response rate was 78%. Moreover, most patients in that study achieved a ≥ 50% PSA response at 3 months. Therefore, we can assume 75% as the PSA response rate at 3 months in the enzalutamide arm. On the other hand, the PSA response rate of flutamide is 35% [9]. The primary efficacy endpoint is PSA response rate at 3 months after the initial treatment. A total of 41 patients per group will provide an 90% power to detect an absolute difference in response rate of 50% (75% vs. 25%) at 2-sided α of 0.05 for superiority test with 5% margin. A dropout rate of 10% is expected; thus, *N* = 50 per group is considered to be adequate.

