Flutamide, a non-steroidal oral anti-androgen, was often used in clinical practice before bicalutamide was approved. Some small, single-arm non-randomized studies suggest a PSA benefit in flutamide as second-line hormonal therapy [5–11]. However, the use of flutamide is optional for limited patients with CRPC according to the American Urological Association guidelines [12] owing to the modest PSA benefit, with PSA declines of > 50% occurring typically in only 20–40% of men with a median duration measured in several months.

Enzalutamide is an androgen receptor inhibitor that targets several steps in the androgen receptor signaling pathway. It inhibits binding of androgens to the androgen receptor, androgen-receptor nuclear translocation, and androgen receptor-mediated DNA binding [13]. In preclinical studies, enzalutamide showed a higher affinity for the androgen receptor and superior suppression of key components of the androgen receptor signaling pathway than bicalutamide [13, 14]. Subsequently, enzalutamide was approved for the treatment of metastatic CRPC based on the results of two pivotal placebo-controlled phase III trials, namely, AFFIRM [15] and PREVAIL [16].

Before the ART era, the treatment options for CRPC are limited, and AAT with flutamide has been widely used in Japan. However, no clinical studies compared AAT with flutamide and enzalutamide as treatment modalities for CRPC. Creating clinical evidence of the superiority of enzalutamide to AAT (bicalutamide to flutamide) in the post-AWS setting in terms of safety and efficacy would be meaningful. To the best of our knowledge, the OCUU-CRPC study is the first randomized head-to-head trial of enzalutamide versus flutamide in patients with CRPC after CAB therapy with bicalutamide.

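### The sample-size paragraph assumes 35% flutamide response but states its power for 75% against 25%; 41 per group and 90% power fit the 35% figure, not the 25% one

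*Protocol article*

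**What the plan says.** All the figures stand in one paragraph of the protocol article, under Calculation of the target sample size.

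- Enzalutamide: "we can assume 75% as the PSA response rate at 3 months in the enzalutamide arm".
- Flutamide: "the PSA response rate of flutamide is 35% [9"], the bracketed number being a citation.
- Size and power: "A total of 41 patients per group will provide an 90% power".
- Effect to be detected: "90% power to detect an absolute difference in response rate of 50% (75% vs. 25"%).
- Test: "at 2-sided α of 0.05 for superiority test with 5% margin".
- Loss: "A dropout rate of 10% is expected; thus", after which 50 per group is called adequate.

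Elsewhere, the Background gives 22% as the response rate of alternative anti-androgen therapy in one cited report. It also describes PSA declines of more than half on flutamide as "occurring typically in only 20–40% of men". Neither place names 25% as the planning value.

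**The concern.** With 75% and 35% as the two assumed rates, the difference is 40 points. The power sentence gives 50 points and a control rate of 25%. The control rate and the difference have both moved, and they agree with each other, so this is not a single mistyped digit. Because 25% lies inside the 20–40% range in the Background, the text alone does not show which rate was meant.

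The planned effect and power are what the primary result will be read against. As printed, the trial seems to need a 50-point difference to have 90% power. If it was in fact sized for 40 points, a true 40-point result could be taken as falling short of the design, and anyone reusing the calculation would start from a wrong set of inputs.

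**Working it through.** **Inputs**, all from the sample-size section: enzalutamide p1 = 0.75; flutamide p2 = 0.25 (power sentence) or 0.35 (stated assumption); margin m = 0.05; two-sided alpha 0.05 (z = 1.960); power 90% (z = 1.282); 41 evaluable per group. Allocation is 1:1 (Treatment section). The article names no formula, so several standard ones were tried.

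**Formulas.** Let D = p1 − p2 − m, V = p1(1−p1) + p2(1−p2), and V0 = 2p̄(1−p̄) with p̄ = (p1+p2)/2. Per group:

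- Unpooled: n = V(1.960+1.282)²/D², where (1.960+1.282)² = 10.507
- Pooled null, unpooled alternative: n = (1.960√V0 + 1.282√V)²/D²
- Fully pooled: n = 10.507·V0/D²
- Continuity correction: n′ = (n/4)[1 + √(1 + 4/(nD))]²

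**Attempt to reproduce the stated figure: 75% against 25%.** D = 0.45, V = 0.1875 + 0.1875 = 0.375, V0 = 0.50.

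- Unpooled: 0.375 × 10.507/0.2025 = 19.5
- Pooled/unpooled: (1.386 + 0.785)²/0.2025 = 23.3
- Fully pooled: 0.50 × 10.507/0.2025 = 25.9
- With continuity correction: 23.7, 27.5 and 30.2

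The Farrington–Manning form gives 23.2. Ignoring the margin lowers the range to 15.8–24.9. Fisher's exact test without a margin first passes 90% at 23 per group. The stated 41 is not reproduced.

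**The same formulas at 75% against 35%.** D = 0.35, V = 0.1875 + 0.2275 = 0.415, V0 = 2 × 0.55 × 0.45 = 0.495.

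- Unpooled: 0.415 × 10.507/0.1225 = 35.6
- Pooled/unpooled: (1.379 + 0.826)²/0.1225 = 39.7
- Fully pooled: 0.495 × 10.507/0.1225 = 42.5
- With continuity correction: 41.1, 45.2 and 48.0

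Farrington–Manning gives 39.6. The stated 41 lies inside this range. No variant rounds up to exactly 41 (41.1 becomes 42), so 41 is consistent with these inputs and not exactly reproduced by them.

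**Power at 41 per group, with the margin.** The unpooled approximation is Φ(D/√(V/n) − 1.960). The exact figure enumerates both binomials and applies a Wald test against the 5-point margin.

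| Rates | Unpooled approximation | Farrington–Manning | Exact |
|---|---|---|---|
| 75% / 25% | Φ(0.45/0.0956 − 1.960) = 99.7% | 99.3% | 99.3% |
| 75% / 35% | Φ(0.35/0.1006 − 1.960) = 93.6% | 91.0% | 92.2% |

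**Power at the planned 50 per group, 75% / 35%:** exact 96.2% with an unpooled variance and 94.9% with a pooled one. At 75% / 25% it is above 99%. With 10% loss, 50 × 0.9 = 45 evaluable; at 75% / 35% that gives 93.4% (Farrington–Manning) to 95.4% (unpooled).

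**Dropout step.** 41/0.9 = 45.6, so 46 per group. Going from 50 to 41 is a loss of 1 − 41/50 = 18%.

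**The case against.** The best defence is that nothing in the trial depends on the slip. Fifty per group exceeds 90% power at either control rate, and the sample size, endpoint and test stay the same whichever rate was meant. Recruitment was due to end in March 2018, before the article appeared in April 2019. A careful reader can also largely infer the intended effect, since 35% is the cited figure and 41 per group fits it. All of this stands, and it limits the consequence to a reporting error. It does not make the power sentence correct, and the inference to 35% comes only by recalculating.

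The dropout step is a weak point by itself. The article calls 50 per group adequate and does not say that it equals 41/0.9, and rounding 46 up to 50 is conservative. It deserves a wording change and no more.

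Three stronger readings are tempting, and the documents do not support them.

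- *The trial is underpowered.* On its own assumptions it is not.
- *75% is too high, because the Discussion reports 60.7% in Japanese patients.* That figure is 17 of 28 patients with metastatic disease and is a confirmed response after bicalutamide and flutamide. It is not given as a 3-month rate. This trial excludes prior flutamide and admits patients without metastases. It is also a different question from the 35%/25% contradiction.
- *41 is a two-arm total*, since 2 × 20 = 40 at 75% against 25%. The words per group, and the 50 per group that follows, rule this out.

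**Conclusion.** The concern holds as an internal contradiction in the stated planning figures. The article gives two control rates, 35% and 25%, and attaches 41 per group and 90% power to the wrong one. With the 5-point margin, 75% against 25% needs about 20 to 30 per group, and 41 gives about 99% power. With 75% against 35%, the requirement is 36 to 43 per group without a continuity correction and up to 48 with one, and exact power at 41 is about 92%.

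This rests on reading the 5% margin as 5 percentage points on the difference in proportions, a two-sided 0.05 test and equal groups. The choice of formula moves the numbers by several patients but does not bring 75% against 25% near 41. That 35% was the intended rate is an inference from the citation and the arithmetic, which only the authors can confirm.

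The size is limited: it is a misstated design figure that should be corrected, not a flaw in the design.

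**What to change.** Confirm the intended flutamide response rate from the original calculation and use it throughout the paragraph.

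- If it is 35%, as cited and as the arithmetic suggests, change the effect to a 40-point difference (75% against 35%) and state about 92% power at 41 evaluable patients per group.
- If it is 25%, correct the earlier 35% with its source and restate the power at 41 per group as about 99%.

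In either case, say that 10% dropout takes 41 to 46 per group and that 50 was chosen by rounding up, which tolerates 18% loss.

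The cost is a correction to one paragraph. Enrolment, endpoint and test are unchanged.

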## Discussion

In the PREVAIL study, enzalutamide significantly reduced the risk of radiographic progression and death by 81% (HR: 0.19; *P* < 0.0001) and 29% (HR 0.71, *P* < 0.0001), respectively, compared with a placebo in chemo-naive men with metastatic CRPC [16]. In this study, 61 Japanese were enrolled (enzalutamide, *N* = 28; placebo, *N* = 33), and most them received more than two types of anti-androgens prior to enrollment, including bicalutamide and flutamide. Even after bicalutamide and flutamide, 17 patients (60.7%) had confirmed PSA responses (≥50% reduction from baseline), and enzalutamide reduced the risk of death by 41% (HR: 0.59; 95% CI: 0.20–1.78) [18]. Japanese patients reported less baseline pain, had less soft-tissue disease, and had lower median PSA at baseline. ADT is more widely used as an initial treatment for early stages of prostate cancer in Japan than in other countries [19]. Before the ART era, the treatment options for CRPC were limited, and AAT with flutamide has been widely used in Japan. Even after enzalutamide and abiraterone were introduced, Bic-CAB as primary therapy and AAT with flutamide as the subsequent therapy for advanced prostate cancer were commonly used in Japan.

In the OCUU-CRPC study, we compare the efficacy and safety of enzalutamide and AAT with flutamide in patients with CRPC who were previously treated with CAB therapy with bicalutamide. Because enzalutamide was superior to bicalutamide in terms of PSA response in patients with CRPC who did not receive any prior bicalutamide or chemotherapy in the TERRAIN and STRIVE studies [20, 21], the expected result of the primary endpoint of OCUU-CRPC study will be that enzalutamide is superior to flutamide in terms of PSA response. A longer time to disease progression with enzalutamide than bicalutamide or flutamide may translate to better overall survival, and enzalutamide may be more effective for men with low-volume disease according to post hoc analysis of the PREVAIL trial [22]. However, AAT with flutamide was particularly effective for patients with CRPC who had long response duration to Bic-CAB [8], and the effect of enzalutamide after AAT with flutamide was preserved [18]. Because enzalutamide and flutamide costs $2478 and $208 ($118 if generic drug) per month in Japan, respectively, AAT with flutamide may be more beneficial and accessible for limited patients owing to its lower cost.

The OCUU-CRPC study has some limitations. The PSA response rate at 3 months without radiographic examinations as the primary endpoint may not be associated directly with overall survival. Moreover, this is not a crossover trial and the treatment after enzalutamide and flutamide is not defined by the protocol. Additionally, because the patients included in this study are Japanese and because flutamide is not commonly used for CRPC in other countries, the findings of the OCUU-CRPC study cannot be generalized and applied to patient populations in other locations or regions.

Currently, a similar clinical trial with enzalutamide and flutamide for CRPC (NCT02918968) is undergoing in Japan, in which the primary endpoint is time to PSA progression with first-line therapy. The result of the NCT02918968 will be published a few years after our result.

## Abbreviations

AAT: Alternative antiandrogen therapy
ADT: Androgen-deprivation therapy
AEs: Adverse events
ALP: Alkaline phosphatase
ART: Androgen receptor targeted therapy
AWS: Antiandrogen withdrawal syndrome
CAB Bic: Combined androgen blockade therapy with bicalutamide
CAB: Combined androgen blockade
CRPC: Castration-resistant prostate cancer
CT: Computed tomography
CTCAE: Common Terminology Criteria for Adverse Events
ECOG-PS: Eastern Cooperative Oncology Group performance status
FACT-P: The Functional Assessment of Cancer Therapy-Prostate
LDH: Lactate dehydrogenase
LHRH: Luteinizing hormone-releasing hormone
PSA: Prostate specific antigen
QOL: Quality of life
RBC: Red blood cell
WBC: White blood cell
